**Patient follow up**

All patients will be closely monitored during the trial as they will have to visit the study site (OPD) daily for assessment and for blood tests (FBC) as standard management of patients with dengue infection. 4ml of blood will be taken at the OPD for FBCs which are done at the hospital (NIID) as standard management of patients with dengue. All patients will attend daily, and assessed for presence of dengue warning signs and the blood pressure and pulse rate will be recorded. During the visits we will find out the day the patient recovers from illness as defined by the following criteria.

Day of recovery is defined when **all three** criteria below are fulfilled:

-Patient afebrile for 24 hours

-Platelet counts of >50,000 cells/mm^3^ or a rise of 20% from the lowest value

-Return of the haematocrit to the patient’s baselineIf the patient need to attend any OPD visits after the day of recovery, they will be paid Rs. 500 as reimbursement for travel. In each visit the patients will be assessed and monitored in an identical manner.

They will be asked to come 14 days after the onset of illness and the patients general wellbeing will be assessed by patient reported outcome measures including presence of any sleep disturbances (Annexure 3). At the 14 day follow up visit, a blood sample will be taken (4ml) and will be assessed for the presence of dengue IgM and IgG specific antibodies at the Centre for Dengue Research (CDR), University of Sri Jayewardenapura.

The patient will also be contacted 30 days after the onset of illness, by phone to assess the general wellbeing and presence of any sleep disturbances. At the follow up an interviewer administered questionnaire will be used to find out the post viral fatigue and sleep disturbances as previously used in similar studies (17-19). The modified fatigue scale has been previously used to evaluate post viral fatigue following West Nile virus infection (19), which is a viral infection similar to dengue. A fatigue questionnaire has been previously used to evaluate fatigue following dengue infection(18). Before administering these questionnaires to patients in this study (annexure 1), we will validate both questionnaires in this country by translating both to Sinhalese and Tamil.

**Blood samples**: 4ml of blood will be obtained at the time of recruitment when the patient is being bled as per routine management of patients with dengue infection and again 14 days later to determine if the patient has primary or secondary dengue. Dengue NS1 will be performed at the OPD itself for with the initial blood sample and dengue virus serotype will be done at the CDR. The antibody testing will be done with the second blood sample at the CDR.

**Dengue virus detection assays**

1. Dengue viral loads will be determined by quantitative real time PCR in all of the patients allocated to each arm of the study. These will be done at the Centre for Dengue Research, USJ.

2. ELISA for dengue antibodies: We will be doing ELISA for dengue IgM and IgG antibodies to determine if the patient is having a primary or a secondary dengue infection on the second sample of blood obtained. As the immune responses are quite different in primary and secondary dengue infections we hope to see if the effects of rupatadine are different in these groups of patients. This ELISA assay has been validated as both sensitive and specific for primary and secondary dengue virus infections (20, 21). The combined use of both IgM and IgG been shown to have a sensitivity of 99% and a specificity of 96% to distinguish between primary and secondary dengue infections(21). Patients who only have dengue virus specific IgM were classified as having a primary dengue (PD) infection while those who had a positive result for both IgM and IgG will be classified as having a secondary dengue (SD infection) (22).

# PARTICIPANT IDENTIFICATION

**Patient recruitment:** Patients with a suspected dengue infection, between the ages of 18 to 60, will be recruited from the OPDs of the NIID following informed written consent.

**Inclusion criteria**: All patients with confirmed dengue infection by a positive dengue NS1 antigen detection test who give informed written consent and who fulfil **all** of the following criteria will be recruited.

- **Age:** between 18-60
- **Duration of illness**: <3 days and who do not show any evidence of vascular leak. This is because in our earlier phase 2 trial, we found that the complications and the reduction in proportion of patients developing DHF was less when given early (3 ≤ days).
- **Evidence of dengue infection:** Dengue NS1 antigen test will be done in these patients and only those who are dengue antigen positive will be included. Although the sensitivity of the NS1 is less in those who are infected with the DENV-2 serotype, and even though those who are NS1 negative can also be having dengue, we will only include those who have are NS1 positive, as we believe it is important to have some evidence that the patient is infected with the dengue virus at the time of recruitment. The virus serotype and the viral loads will be done in all patients at the Centre for Dengue Research (please see below for details).

The dengue NS1 antigen will be done by rapid immununochromatographic assays (rapid strip tests) at the OPD.

**Exclusion Criteria**

- Those who already have fluid leakage
- Fever for >3 days
- pregnant women
- those who have known allergies to antihistamines
- Individuals who are homeless, who are dependent on alcohol dependence or abuse drugs as it will be difficult to monitor these patients in the community
- Those who are unable to take the drugs orally
- Those who have known hepatic impairment defined as: All of the 3 following criteria should be present (16). Patients will be inquired about pre-existing liver disease and their clinical records accessed to find out if they have any of the following.
- Absence of any previously known liver disease
- A prolonged prothromin time of 4-6 seconds or more
- A INR of >1.5
- Those with known renal impairment will be defined as those who fulfill either of the following criteria regardless of age, hypertension and diabetes (23). Patients will be enquired regarding presence of diabetes and hypertension and will be enquired regarding any pre-existing renal disease (annexure 1). Their clinical records will be accessed to determine if they have any of the following.

- predicted GFR <60 ml/min per 1.73 m^2^

- Hereditary kidney disease

- Recurrent or extensive nephrolithiasis

Those with other pre-existing medical conditions that the PI considers may impact on interpretation of the study.

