17 (25.7%) who were assigned to the rupatadine arm and 21 (31.3%) assigned to the placebo arm were recruited at ≤3 days of illness. The overall duration of illness was significantly less in the early treatment group (p=0.03). Of those who were on rupatadine and treated, only one patient (5.9%), developed a pleural effusion, when compared to 6 (12.2%) of those who were recruited later than 3 days (12.2%) (Table 2), but this did not reach significance. Although the proportion of patients who developed ascites was similar, the severity was less in the early treated group in which only one patient (5.9%) developed moderate ascites compared to nine (18.4%) of those who were recruited late. Of those who were recruited early only one (5.9%) patient was given colloids (dextran) in anticipation of subsequent deterioration, when compared to 5 (10.2%) of those who were recruited later. Only one patient (5.9%) had a rise in had the haematocrit rise >20% at some time during the when compared to 8 (16.3%) in the late treatment group.

|  | **Placebo**  **Recruited ≤ 3 days**  **N=21** | **Rupatadine**  **Recruited ≤3 days**  **N=17** | **P value** |
| --- | --- | --- | --- |
| Pleural effusion by Ultra Sound Scan | 3 (14.3) | 1 (5.9) | NA |
| Ascites by Ultra sound scan | 9 (42.8) | 4 (23.5) | 0.3 |
| Extent of Ascites as measured by US Scan  Mild  Moderate | 5 (23.8)  4 (19.4) | 3 (17.6)  1 (5.9) | NA |
| Duration of illness  Median (IQR)  Mean (SD±) | 7 (6 to 8.5)  7.1 (1.8) | 7 (5.5 to 7)  6.3 (1.5) | 0.2 |
| Haematocrit >20% rise from baseline | 4 (19.4) | 1 (5.9) | 0.3 |
| Low platelet counts  <20,000  20,00 to 50,000 | 5 (23.8 )  7 (33.3) | 2 (11.7)  7 (41.2) | NA |
| High ALT (>200 U/L) | 2 (9.5) | 1 (5.9) | NA |
| High AST (>200 U/L) | 6 (28.5) | 1 (5.9) | NA |

**Table 2: Clinical and laboratory features of patients who were on rupatadine on the placebo who were recruited on ≤ 3 days**

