## 8.5 Base line assessment

At the initial visit a detailed clinical history will be taken regarding the clinical features and basic demographic details such as age and gender will be recorded. A details medical history regarding past illnesses such as presence of diabetes, hypertension, hyperlipidaemia, asthma and other allergic diseases along with existing liver and kidney failure will be assessed. Those who have existing liver disease or renal disease will be excluded as defined in exclusion criteria. A detailed medical examination will be done and the temperature, heart rate, blood pressure, presence of hepatomegaly or pleural effusions or ascites will be recorded. After examination they will have a FBC done at the hospital and they will be sent home once they are assessed along with the report. They will be advised to come daily to the OPD for assessment and will be educated to seek admission earlier if they develop persistent vomiting, any bleeding manifestations or feel dizzy.

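### The hepatic exclusion reuses the liver-failure endpoint definition, so on neither available reading does it exclude all patients with existing liver disease; the illness-day limits also need reconciling (minor)

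*Protocol*

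**What the plan says.** **Hepatic exclusion.** The Exclusion Criteria bar "Those who have known hepatic impairment defined as: All of the 3 following criteria should be present". The three items are "Absence of any previously known liver disease", "A prolonged prothromin time of 4-6 seconds or more", and an INR above 1.5. Between the instruction and the list, the same bullet adds: "Patients will be inquired about pre-existing liver disease and their clinical records accessed to find out if they have any of the following". Section 8.5 (Base line assessment) states the purpose: "Those who have existing liver disease or renal disease will be excluded as defined in exclusion criteria". The same three items, with the same literature reference and the same requirement that all be present, define liver failure under Secondary end point (a).

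**Illness-day limit.** The Inclusion criteria require a duration of illness of "<3 days and who do not show any evidence of vascular leak". The Exclusion Criteria list "Fever for >3 days". The early-efficacy part of the Background describes the phase 2 patients who "were recruited at ≤3 days of illness", and the Justification uses the same limit of 3 days or less. The reason given beside the inclusion rule writes the inequality the other way round, so that read literally it means 3 days or more.

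**The concern.** An exclusion for a known condition should be met by people who have the condition. This one lists the absence of the condition as a qualifying item. That item makes sense in an endpoint definition, where it separates new liver failure from old disease. It does not make sense in a rule meant to keep old disease out.

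Two things are at stake. First, the rule decides who is randomised, and section 8.5 says these patients are not meant to be. Second, a patient with known liver disease who is enrolled can never meet Secondary end point (a), because that definition also requires no known liver disease. The patient stays in the denominator without being able to contribute an event.

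The illness-day wording matters less. It leaves room for doubt about patients at exactly 3 days, and it leaves the recruited population slightly different from the one that supplied the planning rates.

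**Working it through.** The plan gives no figure to reproduce on this point; the check is one of logic.

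**Step 1. Hepatic rule.** Let L = known liver disease, P = prolonged prothrombin time as defined, R = INR above 1.5. The bullet supports two rules:

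- *All:* excluded if (not L) and P and R.
- *Any:* excluded if (not L) or P or R.

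| L | P | R | Excluded under *all* | Excluded under *any* | Section 8.5 intent |
|---|---|---|---|---|---|
| yes | yes | yes | no | yes | exclude |
| yes | yes | no | no | yes | exclude |
| yes | no | yes | no | yes | exclude |
| yes | no | no | no | **no** | exclude |
| no | yes | yes | yes | yes | – |
| no | yes | no | no | yes | – |
| no | no | yes | no | yes | – |
| no | no | no | no | **yes** | admit |

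- Under *all*, 1 of 8 combinations is excluded, and 0 of the 4 with known liver disease.
- Under *any*, 7 of 8 are excluded. These include the patient with no liver disease and normal tests, who is the ordinary candidate for this trial. The one combination admitted is known liver disease with normal tests.
- The row common to both failures is known liver disease with normal prothrombin time and INR. It is admitted on either reading.

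**Step 2. Does another section repair the rule?** Section 8.5 states the intent but defers to the exclusion criteria for the definition, so it leads back to the same bullet. Sections 8.2 and 8.5 name a full blood count at the initial visit and no prothrombin time or INR. The bullet relies on clinical records for the test items. The annexures are not shown, so I draw nothing further from this.

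**Step 3. Effect on the endpoint.** Secondary end point (a) = (not L) and P and R. With L true the first term is false, so the endpoint cannot be met whatever the later test results.

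**Step 4. Illness day.** Secondary end point (e) starts illness on the day fever develops, so the inclusion and exclusion limits share one starting point. Counting in whole days:

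| Day | Meets inclusion (<3) | Meets exclusion (>3) | In the ≤3-day phase 2 group |
|---|---|---|---|
| 1, 2 | yes | no | yes |
| 3 | **no** | **no** | **yes** |
| 4, 5 | no | yes | no |

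Only exactly 3 days is affected.

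**Step 5. Link to the sample size.** The section on the number of participants uses 42.8% and 23.5%. Table 2 in the Background gives ascites in 9/21 = 42.86% (printed as 42.8) and 4/17 = 23.5%, in patients recruited at 3 days or less. The planning rates therefore come from a group that includes day 3. The document does not say how many of the 17 + 21 = 38 were at exactly 3 days.

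**The case against.** **The intent is clear and there is a backstop.** The bullet has staff ask about pre-existing liver disease, section 8.5 says these patients are excluded, and the list ends with an exclusion for other pre-existing conditions at the investigator's judgement. All of this stands. Enrolment of patients with liver disease is a risk of the text, not a prediction of conduct. But a judgement clause does not turn a wrong definition into a right one.

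**The rule does not simply exclude nobody with liver disease.** A reader might infer that it can never apply to such a patient. That holds only when all three items are required. Under *any*, known liver disease with an abnormal prothrombin time or INR is excluded. This part of the objection stands, so the claim is limited to what each reading does.

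**The illness-day limits can be applied together.** A reader might infer an outright contradiction. The Inclusion criteria require every criterion to be met, and section 8.1 requires meeting inclusion and having no exclusion. A patient at exactly 3 days fails inclusion and is ineligible. Also, because the day of fever onset counts as the first day, a patient on the third calendar day may have fewer than 3 elapsed days. Both points stand. What remains is that the exclusion list and the rationale imply day 3 is admissible, and that no counting convention is stated.

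**Size.** A reader might take the phase 2 share recruited at 3 days or less, 38 of 66 + 67 = 133 (29%), as the number in dispute. It is the whole early group, not the day-3 patients. Nor do the documents show that the effect differs between those under 3 days and those at 3 days; a strict limit recruits a subset of the early group.

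**Conclusion.** The hepatic exclusion is wrong as written and should be corrected. On neither reading does it do what section 8.5 says. Requiring all three items excludes 0 of 4 combinations with known liver disease. Requiring any one excludes all 4 combinations without it and still admits known liver disease with normal tests. This rests only on the wording of the bullet, section 8.5 and Secondary end point (a). The consequence concerns who is randomised and one secondary endpoint; the definition of the primary endpoint, DHF, does not depend on it.

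The illness-day wording is a minor inconsistency confined to exactly 3 days. The documents do not show that recruiters will in fact differ, since recruitment is from the outpatient departments of one institution; they show only that the text permits it.

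The number of patients affected by either point cannot be derived: the document gives neither the frequency of liver disease among candidates nor a count of day-3 patients.

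**What to change.** 1. Reconcile the hepatic bullet in the Exclusion Criteria with section 8.5, so that the exclusion captures existing liver disease as section 8.5 intends. Remove the conflict between *all* and *any*. Whether and how test results enter the exclusion is for the sponsor to decide.
2. Keep the three-part definition, with its item on absence of known liver disease, for Secondary end point (a) only.
3. In the same edit, reconcile the Justification, the Inclusion criteria (including the reversed inequality in their stated reason) and the Exclusion Criteria to one illness-day limit of the sponsor's choosing. State whether days are counted as calendar days from fever onset or as elapsed time. If the limit chosen leaves out day 3, say in the sample-size section that the planning rates come from a slightly wider group.

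The cost is a few lines in the eligibility lists and in any screening form that repeats them, plus submission to the ethics committee and the regulator's trials subcommittee if the protocol is already approved and the change is substantial. No new data collection follows from the wording change itself. Its effect on recruitment cannot be stated from the document.

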# TRIAL PROCEDURES

## 8.1 Recruitment:

Patients, who are suspected to be having a dengue infection, who fulfil the inclusion criteria and who do not have the exclusion criteria will be approached by a member of the team of investigators or by a medical officer of the unit who will be specially trained in obtaining proper consent.

Once consent is given, they will be tested for dengue NS1 antigen test. These tests will be done free of charge for all patients with suspected dengue infection at the OPD of the hospital. The patients who are confirmed to be having acute dengue infection and they will be recruited to the study.

## 8.2 Screening and Eligibility Assessment

At the initial visit they will be assessed for the presence of dengue warning signs, their blood pressure and pulse rate recorded and a base line FBC done. If the patient is found to have evidence of fluid leakage or fulfil any of the exclusion criteria in the assessment, he/she will not be recruited.

## 8.3 Informed Consent

Consent will be taken by one of the investigators in the team, who have completed GCP training. The patients will be given the patient information sheets of the study and will be given an opportunity to discuss their concerns/questions with a member of the team of investigators. Once the patient is satisfied with the information given to him/her, he/she will be given the opportunity to join the study or to decline. They will be made aware that their decision will in no way affect their other treatment, and that they are free to withdraw at any time.

## 8.4 Randomisation, blinding and code-breaking

The randomization schedule will be designed by the statistician and she will be responsible for providing the randomization codes. The tablets of the placebo and the rupatadine will be packed into envelops, which is to be given to each patient. Each envelop will contain tablets needed for the whole duration of treatment (5 days). Once the codes are provided, the packaging will be by individuals who are not involved in the study. The packed and sealed envelopes will be stored at the Centre for Dengue Research and released in small batches to be given to patients. A person who is not involved in the study will be responsible for dispersing these envelops. Therefore, all investigators and the patients will be blinded.

Once the patients are enrolled to the study a serial number is assigned in a chronological order for data entering purposes. Total number of patients will be 262 and all will be treated according to the current Dengue guidelines published by the Ministry of Health, Sri Lanka. The study groups will receive 40 mg of rupatadine in addition to the treatment guidelines (please see below). The two treatments would be named A (40mg rupatadine) and B (placebo). The patients will receive either 4 tablets of rupatadine daily for 5 days or 4 tablets of the placebo for 5 days, which will be prepacked in an envelope containing the code number. This code number will be entered in the data collection sheet along with the patient’s serial number.

Randomization will be done by using a random number table (1-10). Using this table an arbitrary point would be chosen, and the patient would be allocated according to the random number. If the number selected from the random table is between 1 to 5, the patient would be assigned to the treatment arm A. If the number selected from the Random table is between 6 to 10. The assignment information will be kept under lock and key. Neither data collectors nor the patients will be made aware of the randomization at any given point of time.

The codes will be kept with the PI and in the event of a SAE or a SAR the codes will be broken. The codes can be accessed all 24 hours. However, since we have already carried out a phase 2 trial to determine the safety of rupatadine 40mg, and was found to be safe, we do not expect any SAE. In addition, rupatadine 40mg has been used in many countries for the treatment of allergic rhinitis and chronic urticaria and SAR or SAE have not been reported.

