# SYNOPSIS

| Trial Title | The efficacy of rupatadine in treating dengue: a randomised, double blinded, placebo controlled trial | |
| --- | --- | --- |
| Short title | Efficacy of rupatadine in dengue | |
| Clinical Phase | Phase 2 | |
| Trial Design | Randomised, double blinded, placebo controlled | |
| Trial Participants | Patients with dengue infection | |
| Planned Sample Size | 280 with 140 each in each study arm | |
| Treatment duration | 5 days | |
| Follow up duration | 30 days of illness | |
| Planned Trial Period | 1 year | |
|  | Objectives | Outcome Measures |
| Primary | To determine the proportions of dengue patients who develop DHF when treated with and without rupatadine | Therefore, the reduction of the proportion of individuals who develop fluid leakage (DHF) will be assessed.  Evidence of plasma leakage: evidence of plasma leakage considered as detection of free fluid in the abdomen or by the presence of a pleural effusion by USScan and/or by the presence of a rise in haematocrit of >20% of the baseline. |
| Secondary | Investigate whether rupatadine treatment leads to a. reduction in complications such as liver failure.  b. Reduction in development of shock:  c. Need of colloids:  d. Need of blood transfusion/s:  e. Duration of the illness.  f. Sleep disturbance | Liver function tests, blood clotting, colloid infusion volumes, blood transfusion volumes, length of acute illness, sleep scores. |
| Investigational Medicinal Product(s) | Rupatadine 40mg | |
| Formulation, Dose, Route of Administration | Four 10mg tablets of rupatadine to be given orally, and placebo | |

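### All investigators are declared blinded, yet the PI holds the allocation codes and no independent custody or individual sealing is described

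*Protocol*

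**What the plan says.** Protocol section 8.4 (Randomisation, blinding and code-breaking) has the statistician prepare the schedule. People outside the study pack numbered envelopes, and another uninvolved person hands them out. From this it concludes: "Therefore, all investigators and the patients will be blinded".

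The same section makes three further statements that bear on custody:

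- On storage: "The assignment information will be kept under lock and key". It does not say who has the key.
- On who is kept unaware: "Neither data collectors nor the patients will be made aware of the randomization at any given point of time". This group is narrower than all investigators.
- On custody and emergency access: "The codes will be kept with the PI", to be broken at a serious adverse event or serious adverse reaction. The codes are to be reachable at any hour.

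The Exclusion Criteria end with a judgement reserved to the PI: "Those with other pre-existing medical conditions that the PI considers may impact on interpretation of the study".

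On the method of allocation, section 8.4 uses a table of random numbers from 1 to 10: "If the number selected from the random table is between 1 to 5, the patient would be assigned to the treatment arm A". The next sentence, on numbers 6 to 10, stops before naming an arm. The Synopsis plans "280 with 140 each in each study arm", while section 8.4 gives a total of 262.

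**The concern.** Outside packing and dispensing keep the investigators blind only if the key to the codes is also outside their reach. Section 8.4 gives that key to the most senior investigator. A reader of the trial report could not tell from the protocol whether the PI was blinded.

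Two things are at stake:

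- **Blinding of enrolled patients.** The envelope's code number is entered on the data sheet beside the patient's serial number, and section 9.4 logs each envelope issued. Whoever holds the codes can look up the arm of any enrolled patient.
- **Allocation concealment.** The PI may exclude patients at discretion. If the PI could also learn which envelope comes next, selection could be influenced. The protocol does not establish that the PI could learn this, so concealment is possibly exposed rather than shown to be.

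The protocol does not keep the PI away from patients or data either. The Source Data section has the data obtained by interview by one of the investigators, without excluding the PI.

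**Working it through.** **1. Custody: the statements side by side**

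| Question | What section 8.4 gives |
|---|---|
| Who is blinded? | All investigators and patients (first paragraph); data collectors and patients only (end of the randomisation paragraph) |
| Who holds the codes? | The PI, available 24 hours |
| What stops the holder reading them? | Locked storage; no keyholder named |
| Are codes sealed one per patient? | Not stated |
| Is any holder outside the team? | Not for the codes; only for packing and dispensing |

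The first two rows cannot both hold unless the codes are sealed or held in a way that keeps the PI unaware. No such arrangement is described.

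**2. How often the codes might be opened**

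Section 8.4 breaks codes at a serious adverse event (SAE). Section 10.1 counts inpatient hospitalisation as an SAE, and Primary Study Endpoints has every patient with suspected leakage admitted. The rates in The Number of Participants are 42.8% and 23.5%. With 140 per arm:

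140 × 0.428 + 140 × 0.235 = 59.9 + 32.9 = 92.8, or about 93 of 280 patients.

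This assumes that every leakage patient is admitted and every admission is handled as an SAE. Section 8.4 itself expects no SAEs, so the sponsor may not intend this reading, and the sections need to be reconciled. If it were applied, codes would be opened often, and unsealed codes kept together would expose other patients at each break.

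**3. Arm sizes under the allocation rule as written**

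Inputs: N = 280 (Synopsis); probability 0.5 for arm A (numbers 1 to 5 of 10; arm B is assumed for 6 to 10); no block, stratum or cap described. Arm size is then Binomial(N, 0.5).

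- Mean = 280 × 0.5 = 140, which reproduces the planned figure as an average.
- SD = √280 / 2 = 8.4.
- P(exactly 140/140) = 4.8%.
- 95% range = 124 to 156.
- P(an arm is 10 or more away from 140) = 26%; 20 or more away = 2.0%.

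With section 8.4's own total of 262, the mean is 131, the SD 8.1 and the 95% range 115 to 147.

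**4. What the imbalance costs**

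Assumptions: the protocol's two rates, two-sided 5% level (sidedness is not stated), no dropout, normal approximation with pooled variance under the null:

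Power = Φ[(Δ − 1.96 × SE₀) / SE₁], Δ = 0.428 − 0.235 = 0.193.

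- 140/140: SE₀ = √(2 × 0.3315 × 0.6685 / 140) = 0.0563; SE₁ = √[(0.428 × 0.572 + 0.235 × 0.765) / 140] = 0.0551. Power = Φ(1.50) = 93.3%.
- 124/156: 93.1% or 93.0%, depending on which arm is smaller.

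The loss at the edge of the 95% range is about 0.3 percentage points.

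**The case against.** The strongest reply is that the protocol shows access and nothing more. It speaks of codes, not of an open list, and it keeps assignment information locked. Envelopes are released in small batches and handed out by someone uninvolved. The chronological serial number serves data entry and is distinct from the code number. Nothing says that envelopes go out in code order, so the PI is not shown to know the next allocation. No section gives the PI the decisions on admission or dextran: Concomitant Medication refers to treating physicians, and the secondary endpoints tie dextran to national guidelines. Leakage is defined by haematocrit or ultrasound, with scans re-read by a radiologist. The PI's own exclusion covers pre-existing conditions only.

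All of this stands, and it narrows the route to bias. It does not reconcile the blinding statement with the custody statement, and the discretionary exclusion remains.

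Three stronger readings are tempting, but the documents do not support them:

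- **That the design cannot deliver 140 per arm.** It averages 140 and can reach it by chance. It does not guarantee it, and the cost is trivial.
- **That permuted blocks are needed.** Simple 1:1 randomisation is valid and is the least predictable scheme. Blocking is a preference.
- **That naming A as rupatadine and B as placebo decodes labels seen on site.** Sections 8.4 and 9.4 put a number on the envelope. Nothing puts A or B on an envelope or site form.

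**Conclusion.** The point holds on custody. Section 8.4 declares all investigators blinded and places the codes with one of them, with locked storage as the only safeguard described. Blinding of the PI, and possibly allocation concealment, depends on restraint rather than on procedure.

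A reader might infer that the PI will look, or that the trial is in effect unblinded. The documents do not support either inference, and they give no basis for putting a size on any bias. The conclusion assumes only that no sealing or outside custody exists beyond what the protocol describes.

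The allocation method is a minor note: about 0.3 points of power at 124/156, under the assumptions shown. The sentence on numbers 6 to 10 is incomplete and needs an arm. This is worth correcting by amendment, chiefly for custody.

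**What to change.** Amend the code-breaking paragraph of section 8.4 so that:

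- a named role outside the study team holds the codes, with 24-hour emergency access kept;
- there is one sealed code per envelope number, so that a break reveals one patient only;
- the blinding statement names the same group throughout, with the PI included.

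In the same amendment, finish the sentence on numbers 6 to 10 and bring the total in section 8.4 (262) into line with the Synopsis (280). If simple randomisation is kept, describe 140 per arm as the expected size.

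The cost is small. The plan already relies on uninvolved packers and an uninvolved dispenser, so an outside keyholder fits the existing arrangement. The one practical burden is arranging round-the-clock cover outside the team. Sample size, treatment and analysis are unaffected.
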